### Secondary outcomes

*The Major Depression Inventory* (MDI) by Olsen et al. (2003) [47] consists of a 10-item questionnaire measuring parental symptoms of depression on a six-point scale. The wording of the questions can be found in Olsen et al. (2003).

*The Mother and Baby Interaction Scale* (MABIC) by Hackney (1996) [50] consists of a 10-item questionnaire measuring the mother-infant relationship on a five-point Likert scale. The wording of the questions can be found in Hackney (1996).

*The duration of exclusive breastfeeding and any breastfeeding* according to the definition of the WHO [51] is measured in the weeks following birth.

*The Ages and Stages Questionnaire: (ASQ-3)* by Squires et al. (2016) [52] is a 21-item questionnaire measuring communication, gross motor skills, fine motor skills, problem solving and personal-social competencies in children aged from 1 month to 5 years. The ASQ is rated by parents on a three-point scale [49]. The wording of the questions can be found in Squires et al. (2016).

*The Strengths and Difficulties Questionnaire (SDQ)* by Goodman (2001) [53] consists of a 25-item questionnaire and measures five domains: hyperactivity, peer problems, conduct problems, emotional symptoms and pro-social behaviours rated by parents on a three-point scale. The wording of the questions can be found in Goodman (2001).

### Background information and mother, father and infant characteristics

Data collected on the background characteristics of mothers, fathers and infants include: parental age, gender, marital status, educational level, employment status, smoking habits, height and weight, well-being WHO-Five [54] and Coupes Satisfaction Index [55]. Concerning the infant: place of birth, gestational age, and questions about infant development. Supplemental data collected from the services received from health visitors and medical services include infant contacts to GP, the emergency room and hospitals within the first year of life.

Background socioeconomic information on eligible parents who do not enrol in the study is available from register data. This allows for comparison of participants in the randomised groups with the overall population, and for examination of the heterogeneity of programme effects across family types.

### Data collection health visitors

Data from health visitors are collected at three time points: Before the NBO training course in October 2016 (only the health visitors of the intervention group), before the intervention period in December 2016 and after the intervention period in February 2018. Self-reported questionnaires are obtained via printed questionnaires; and measures include: *Observation skills:* The ability to observe the quality of parent-infant interactions was measured by asking the health visitors to observe and assess four video-recordings on mother-infant interactions regarding the mother’s sensitivity and the mother-infant dyadic synchrony [48]. *Knowledge about early relationship:* Infant’s signs of stress, emotional self-regulation and how to comfort an infant were measured by asking health visitors about their general knowledge in a four-item questionnaire. *Intention:* Valuation of personal goals for working with early relationships was measured by one question and rated on a Likert scale. *Self-efficacy:* Confidence in the ability to work with early relationships and skills in supporting and guiding and capacity to cope with insecure first-time mothers to establish a healthy relationship with their newborn infants were measured using a 12-item questionnaire. *Background information and characteristics of the participating health visitors:* data on age, work experience and additional education and training.

### Sample size

Ongoing research shows that 25% of new mothers have a risk score < 40 on the KPCS [28]. Building the power calculation on an assumed loss to follow-up of 15%, a significance level of 5% and a power of 80%, calculations showed a need for 934 participating mothers to be able to identify a statistically significant difference decrease of 8% in reporting low confidence in understanding their infants. Taking an average of the relatively large cluster size into account (1 + (cluster size-1)*ICC), the desired number of participating mothers will be 934 X (1 + (200–1)*0.01) = 2793 mothers [56]. The included intraclass correlation coefficient (ICC) in the calculation is relatively low because the self-reported outcome is collected individually, and we do not expect mothers within clusters to be more alike than mothers across clusters. Moreover, earlier findings in similar research have shown a low cluster effect [35]. With the current birth rate in the participating municipalities, the number will require an inclusion and project period of approximately 12 months with follow-up at 3, 9 and 18 months.

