**Methods:**

This is a cluster-randomised community-based study implemented in four Danish municipalities. Health visitors will conduct the trial, and the geographical districts they work in will constitute the clusters as units of randomisation. The participants will be approximately 2800 new families, randomised into an intervention or a comparison group according to their health visitor. The families are recruited at the first postpartum home visit. Parents in both groups receive care as usual: parents in the intervention group also receive the standardised NBO method in home visits performed from 3 weeks to 3 months postpartum. Data consist of self-reported parent questionnaires and video recordings of a selected group of vulnerable first-time mothers recorded 4 months postpartum. The self-reported data are obtained: at baseline 1 week postpartum and then at follow-up 3, 9 and 18 months postpartum. Data will be analysed using the intention-to-treat method and the analyses will include comparison of change in the primary variables across time supplemented by multiple regression analysis. The primary study outcomes are measured by the following factors: parental confidence, infants’ socio-emotional development and mother-infant relationship. Other measures include parental mood and stress, breastfeeding duration and utility of the health visitor services. Data collection among the health visitors in both groups will serve to monitor any change in practice regarding the work with early parent-infant interactions.

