### Randomisation

The cluster randomisation was carried out in June 2016 after receiving the declaration about participation from the municipalities and before the health visitors’ enrolment in the NBO training course. The already established geographical districts within the four participating municipalities where health visitors provide home visits to new families were regarded as clusters (*n* = 17) to avoid a spill-over effect between health visitors and families. Thus, health visitors were allocated to an intervention or comparison group according to their geographical districts, whereas the participating families were allocated according to their health visitor.

Prior investigation of the clusters alias the districts revealed that all districts represented a variation in social status among inhabitants and considerable differences in birth rates; in 2015, from 50 to 200 births. The birth rates were associated with the number of health visitors employed in each district. Because of the relatively small number of clusters, we therefore decided to use a restricted randomisation procedure to achieve balance between the two study arms [57]. The criterion for the restricted randomisation was a geographical balance with all participating municipalities represented by both intervention and comparison districts. Moreover, we attempted to obtain numerical balance with the expected number of births between the intervention and the comparison group. In each municipality, the districts were divided into two groups. For each municipality, the districts were allocated randomly to one of the two treatment groups ensuring that both treatments appeared in each municipality and that the treatment groups had approximately the same expected number of births as the comparison groups. An independent data manager handled the entire randomisation procedure.

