### Statistical methods

Our data analyses will be in accordance with the CONSORT guidelines [58]. Intention to treat analysis will be used to detect the effect of the community-based intervention where participation may vary in the study population of parents. Following the intention to treat principle, mothers and fathers will remain in the group defined by the cluster randomisation. A baseline comparison of pre-defined background variables in the two groups will include unpaired t-tests and Fisher’s exact test. When testing the NBO with treatment as usual, the mean scores and any change in the primary variables across time in the intervention group from pre-test (at 2 weeks) to post-test at3, 9 and 18 months will be compared to mean scores and changes in the comparison group. Supplemental analyses will be performed to identify an intervention effect for subgroups and marginal groups of parents according to parity, preterm delivery and depression symptoms. Analyses will include multiple regression analysis to adjust for pre-randomisation variables such as parents’ age, marital status and educational background. Due to the small number of clusters, the analysis will include adjustment for within-cluster correlation. As we examine a relatively large number of outcomes, we will assess the robustness of our findings by applying methods suitable for multiple hypotheses testing. Finally, we will perform a drop-out analysis and examine the comparability of intervention and comparison group in the trial with respect to differences in received health visitor services.

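### The sample size is powered on the proportion of mothers with KPCS < 40 in one 5% test, but the plan compares mean scores and changes on three primary outcomes, so the stated 80% and 5% do not describe the primary analysis.

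*Protocol article*

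**What the plan says.** **Sample size section.** The starting point is that "Ongoing research shows that 25% of new mothers have a risk score < 40 on the KPCS". The trial is sized to "identify a statistically significant difference decrease of 8% in reporting low confidence in understanding their infants", with 80% power, a 5% significance level and 15% loss to follow-up. Clustering then gives "934 X (1 + (200–1)*0.01) = 2793 mothers". The calculation concerns mothers only and names no visit.

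**Primary outcomes.** The abstract says "The primary study outcomes are measured by the following factors: parental confidence", and goes on to infant socio-emotional development and the mother-infant relationship. The Primary outcomes section matches these to KPCS, ASQ:SE and the CARE-Index video, which yields three scores.

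**Statistical methods section.** The comparison is of "the mean scores and any change in the primary variables across time in the intervention group from pre-test (at 2 weeks" to 3, 9 and 18 months against the same quantities in the comparison group. No analysis of the proportion below 40 is described; Fisher's exact test appears only for baseline variables. On multiplicity, the section says "we will assess the robustness of our findings by applying methods suitable for multiple hypotheses testing".

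**Table 1.** KPCS is collected at 2 weeks, 3 months and 9 months, but not at 18 months. The CARE-Index is collected once.

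**The concern.** A power statement is useful when it describes the test that decides the trial. Here the powered test is a single comparison of two proportions in mothers. The described analysis compares means and changes, on three outcomes with equal primary status. A reader of the final report could not tell which result the 80% refers to, or what overall error rate protects the primary claim.

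The multiplicity sentence does not close the gap. It names a check on findings, not the rule by which a primary outcome is declared positive, and the sample size uses the whole 5% once. The change schedule also fits only ASQ:SE fully: KPCS has no 18-month value, and the CARE-Index has no pre-test from which to measure change.

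**Working it through.** **1. Which test was powered?**

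Inputs from the Sample size section: 25% control rate, 8-point decrease (so 17%), alpha 0.05, power 80%. Two-sided testing and equal arms are assumed; the Randomisation section supports the latter, since "the treatment groups had approximately the same expected number of births as the comparison groups".

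With pooled rate 0.21:

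- 1.960 × √(2 × 0.21 × 0.79) = 1.129
- 0.842 × √(0.25 × 0.75 + 0.17 × 0.83) = 0.482
- n per arm = (1.129 + 0.482)² / 0.08² = 405.7, so 406, or 812 in total
- 812 × 1.15 = 934, the stated figure (812 / 0.85 would give 956)
- 934 × 2.99 = 2792.7, so 2793, the stated figure

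Both figures reproduce. Reading the 8% as relative (25% to 23%) would need about 16,500 mothers before clustering, so it is excluded. The powered test is binary, in mothers, at an undivided 5%.

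**2. Effective size.**

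The plan's own route gives 406 per arm. Taking 15% off 2793 and dividing by the design effect gives 2793 × 0.85 / 2.99 / 2 = 397 per arm. About 400 is used below.

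**3. Error rate with three primary outcomes, each at 5%.**

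- Independent: 1 − 0.95³ = 14.3%
- Common correlation 0.5 (assumed, simulated): about 13%
- Common correlation 0.7 (assumed, simulated): about 11%

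These figures take one test per outcome. Separate tests by visit, parent or CARE-Index scale would raise them.

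**4. Power if the proportion is the primary comparison.**

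| Alpha | 406 per arm | 397 per arm |
|---|---|---|
| 0.05 | 80% | 79% |
| 0.05/3 | 66% | 65% |

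Holding 80% at 0.05/3 would need 542 per arm. With the plan's own inflation this is 1084 × 1.15 × 2.99 = about 3727 mothers.

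**5. Power if the mean is the primary comparison.**

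The document gives no KPCS standard deviation or target mean difference. Detectable difference at 80% power with 397 per arm, on normal quantiles:

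- alpha 0.05: (1.960 + 0.842) × √(2/397) = 0.20 SD
- alpha 0.05/3: (2.394 + 0.842) × √(2/397) = 0.23 SD

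To link the two scales, assume normal scores with equal SD and a pure shift. Then 25% to 17% is a shift of 0.954 − 0.674 = 0.28 SD. The standardised effect is 0.28 × √(397/2) = 3.94.

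| Alpha | Normal | t, 15 df (17 clusters − 2) |
|---|---|---|
| 0.05 | 98% | 96% |
| 0.05/3 | 94% | 88% |

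**The case against.** The strongest reply has three parts.

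*Only a condensed article is shown.* The primary visit, the named adjustment and the family of tests are commonly left to the full protocol or SAP. This largely stands: an unnamed method is not in itself a fault here. But a SAP can only add detail. It cannot make a binary, single-test calculation describe the comparison of means that this document sets out.

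*Multiplicity is acknowledged.* It is, and the text does not state that each outcome will be declared positive at an unadjusted 5%. What it does state places the adjustment among robustness checks, and nothing in the sample size allows for it. The error rates above are therefore conditional on testing each outcome at 5%.

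*The mismatch may do no harm to KPCS.* This stands, subject to the normal-shift assumption, for which the document offers no support. A reader might infer that KPCS is underpowered. The document does not show that; on this assumption the mean comparison has more power than the 80% stated.

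A reader might also count every parent, visit and scale separately (KPCS 4, ASQ:SE 6, CARE-Index 3) and infer a 49% error rate from 1 − 0.95¹³. The document lists no such set of 13 tests, and its wording also fits one longitudinal model per outcome. The measures would be clearly correlated as well: at assumed common correlations of 0.7 to 0.3 the figure is about 24–42%. The 49% should not be quoted as the plan's error rate.

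**Conclusion.** The conflict is real and lies within the document. The 934 and 2793 come from a two-proportion test of KPCS < 40 that the Statistical methods section does not include, and the single 5% does not match three primary outcomes. The consequence is an error rate of about 11–14% instead of 5% for one test per outcome, if each is tested at 5%. That range covers assumed correlations from 0.7 down to none.

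The finding is that the stated power and error rate are not tied to the planned analysis. It is not that the trial is too small. All power figures take the document's design effect of 2.99 as given. Normal-quantile figures ignore the loss from having only 17 clusters; the 15-df figures allow for it.

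**What to change.** 1. Reconcile the Sample size and Statistical methods sections. State which form of maternal KPCS (mean score or proportion below 40) is the powered primary comparison and at which measured visit, 3 or 9 months. Include that cluster-adjusted test in the analysis and restate power for it:
   - mean: about 0.20 SD detectable at 80% power and 5%, or 0.23 SD at 0.05/3, with about 400 effective mothers per arm;
   - proportion: about 80% power at 5%, or about 66% at 0.05/3.
2. If all three outcomes stay primary, prespecify one test per outcome and apply a familywise adjustment such as Holm in the primary analysis, not as a robustness check.

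Making ASQ:SE and the CARE-Index secondary would also settle the error rate, but that is a design choice and is not required.

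No new data or recruitment is needed. The cost is somewhat less favourable power or adjusted p-values. Recruitment began on 1 January 2017, so the change should be recorded as a dated amendment and checked against the trial registration.

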### Randomisation

The cluster randomisation was carried out in June 2016 after receiving the declaration about participation from the municipalities and before the health visitors’ enrolment in the NBO training course. The already established geographical districts within the four participating municipalities where health visitors provide home visits to new families were regarded as clusters (*n* = 17) to avoid a spill-over effect between health visitors and families. Thus, health visitors were allocated to an intervention or comparison group according to their geographical districts, whereas the participating families were allocated according to their health visitor.

Prior investigation of the clusters alias the districts revealed that all districts represented a variation in social status among inhabitants and considerable differences in birth rates; in 2015, from 50 to 200 births. The birth rates were associated with the number of health visitors employed in each district. Because of the relatively small number of clusters, we therefore decided to use a restricted randomisation procedure to achieve balance between the two study arms [57]. The criterion for the restricted randomisation was a geographical balance with all participating municipalities represented by both intervention and comparison districts. Moreover, we attempted to obtain numerical balance with the expected number of births between the intervention and the comparison group. In each municipality, the districts were divided into two groups. For each municipality, the districts were allocated randomly to one of the two treatment groups ensuring that both treatments appeared in each municipality and that the treatment groups had approximately the same expected number of births as the comparison groups. An independent data manager handled the entire randomisation procedure.

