### Health visitors, implementation and adherence

All authorised health visitors employed in the four participating municipalities who conduct home visits with new families are eligible and will be included in the study. In June 2016 before project start, participating health visitors were randomised to either the intervention or the comparison group according to their geographical districts.

In October 2016, all health visitors working in districts randomised to the intervention group received a 2-day NBO training course by certified NBO trainers followed by a training phase in which the health visitors practiced and completed a minimum of five NBO recordings before achieving their NBO certification in December 2016. A number of strategies ensured that the delivery of the NBO was in line with the standardised version. Firstly, each health visitor received a manual on the NBO method for the training course, and all health visitors joined a 1-h team Skype session twice during the training phase. Secondly, teams of health visitors from the intervention group participated in a 1-day workshop in March 2017 and also in a 2-h supervision session every third month during the intervention period. The general aim of these strategies was to motivate health visitors and facilitate the delivery of the NBO method by giving the health visitors an opportunity to ask questions and achieve feedback.

A linkage group was established at the beginning of the project consisting of the health visitor leaders from each of the four participating municipalities, the NBO trainer and the scientific investigators. The aim of this group is to coordinate and facilitate communication and involvement between the fields of practice and researchers. The group meets every 4 months during the planning and intervention period.

The delivery and thus the degree of implementation of the NBO intervention is continually registered by health visitors in the intervention group as they fill in a checklist during each home visit performed 3 weeks after birth to monitor which parts of the NBO was delivered during the visit. Additionally, data collection among the health visitors in both the intervention and comparison group aims at following any change in the health visitors’ knowledge, observation skills, intention and self-efficacy in their work with early parent-infant interactions.

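### The Randomisation section leaves the allocation unit ambiguous (district, or pre-formed group of districts), and the stated analysis does not reflect the restriction by municipality and expected births

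*Protocol article*

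**What the plan says.** The Abstract states that "the geographical districts they work in will constitute the clusters as units of randomisation". The Randomisation section counts 17 such districts in four municipalities, with 50 to 200 births each in 2015, and explains that a restricted procedure was chosen because there were few clusters. It then gives two consecutive sentences: "In each municipality, the districts were divided into two groups. For each municipality, the districts were allocated randomly to one of the two" arms, under the conditions that every municipality contributes to both arms and that expected births are similar between arms. It does not say how the two groups were formed, whether they are the same thing as the two arms, or how many allocations were possible. The Discussion concedes that clustering and restriction made the allocation less random, but gives no number.

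For the analysis, the Statistical methods section says "Due to the small number of clusters, the analysis will include adjustment for within-cluster correlation". The adjustment variables it gives as examples are parental age, marital status and education. It mentions neither municipality nor expected births.

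**The concern.** The randomisation fixes which units could have ended up in different arms, and the analysis should follow that. If each municipality's districts were first put into two fixed groups and one group was then drawn for the intervention, districts in the same group could never be separated. Anything they share would then be confounded with arm within that municipality, and an adjustment for correlation within district would not capture it. There would be eight allocation units in four pairs.

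If single districts were drawn under constraints, the unit is the district, but the draw was still restricted by municipality and by expected births. The analysis should reflect those two restrictions on either reading, and the variables named in the article do not include them. At stake are the validity of the p-values and intervals for the primary outcomes and, on the group reading only, the stated power.

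**Working it through.** **Plan's own figure.** Inputs from the Sample size section: "25% of new mothers have a risk score < 40 on the KPCS"; a "statistically significant difference decrease of 8% in reporting low confidence in understanding their infants", read as 25% to 17%; "a significance level of 5% and a power of 80" per cent; "assumed loss to follow-up of 15" per cent. A two-sided test is assumed.

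- Per arm: n = [1.96·√(2·0.21·0.79) + 0.842·√(0.25·0.75 + 0.17·0.83)]² / 0.08² = 405.7, so 406.
- Loss: 406 × 1.15 = 466.9, so 467 per arm and 934 in total. This matches.
- Design effect: 1 + 199 × 0.01 = 2.99, and 934 × 2.99 = 2792.7, so 2793. This matches.

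The number of clusters, or of draws, does not enter this formula.

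**Number of allocations.**

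- Group reading: one binary draw in each of four municipalities gives 2^4 = 16. Each allocation and its mirror image give the same absolute difference, so the smallest two-sided p-value is 2/16 = 0.125.
- Single-district reading: the number of districts per municipality is not given. Assuming 4, 4, 4 and 5, and requiring both arms in each, there are (2^4 − 2)^3 × (2^5 − 2) = 14^3 × 30 = 82,320 allocations before the birth constraint. With near-even splits only, there are 6^3 × 20 = 4,320.

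**Power by unit of analysis.** Analysed mothers: 2793 × 0.85 = 2374. Effective number per arm = 2374 / design effect / 2. The standard error is √(0.3286 / effective number), where 0.3286 = 0.25·0.75 + 0.17·0.83. The noncentrality is 0.08 divided by that standard error, and district effects are taken as independent.

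| Design effect | Effective n per arm | Noncentrality | 3 df (4 pairs) | 12 df (17 − 4 − 1) | 15 df (17 − 2) |
|---|---|---|---|---|---|
| 2.99 (plan's cluster size of 200) | 397 | 2.78 | 48% | 72% | 74% |
| 2.39 (2374/17 = 140 per district) | 497 | 3.11 | 56% | 81% | 83% |

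Other ways of handling loss and cluster size give 52% to 58% at 3 df. Applying ICC 0.01 to the eight groups as clusters gives 39% to 40%.

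**False-positive rate, group reading only.** Simulation of a district-level t-test with municipality in the model (12 df), with 20,000 runs per scenario, municipalities of 4, 4, 4 and 5 districts assumed, ICC 0.01 and 140 mothers per district:

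| Share of between-district variance common to a group | 0 | 25% | 50% | 75% | 100% |
|---|---|---|---|---|---|
| False-positive rate | 5.1% | 7.3% | 10.7% | 14.3% | 18.6% |

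A four-pair t-test stays at about 5% throughout. No passage gives the shared fraction, so these rates are conditional.

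**The case against.** A reader might infer that the trial made four binary draws and that its 17-district inference and 80% power are therefore overstated. The documents do not support that as fact.

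- **Group allocation is an inference.** The second sentence makes districts, not groups, the object of the random allocation, and attaches both restrictions to that step. The first sentence may only introduce the second. The Discussion's remark that every district was equally likely to receive the intervention fits either reading.
- **Balance on births is stated for the arms.** It is described as something attempted between arms, not as a property of the two groups within a municipality.
- **False-positive inflation needs shared variance that is not documented.** With none shared, the district-level test with municipality in the model holds its size. The section on health visitors, implementation and adherence reports that "teams of health visitors from the intervention group participated in a 1-day workshop in March 2017", but those teams are not said to match allocation groups. The training followed allocation, in one arm only, and would exist under either scheme.
- **The 80% does not rest on 17 randomised units.** The formula ignores the number of clusters, and with 17 districts the figure is roughly met. The floor of 0.125 binds only a randomisation test, and the 3-df power only a pair-level analysis. The plan proposes neither.
- **An article may leave model detail to the SAP,** and its list of covariates is given as examples.

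All of this stands, and it limits the point to the ambiguity and to the restriction missing from the stated analysis. It does not remove them. The randomisation was complete when the article was written, the article sets out to describe it, and its two sentences admit designs that differ in their number of possible allocations by orders of magnitude.

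**Conclusion.** The point holds as a clarification with consequences for the analysis. The Randomisation section does not establish whether districts or pre-formed groups of districts were allocated. On either reading, the analysis as stated covers within-district correlation and parent characteristics but not the restriction by municipality and expected births.

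The size depends on the answer. If single districts were drawn, the district is the right unit, power is about 72% to 83%, and what remains is to carry the restriction into the analysis. If groups were allocated, there are 16 allocations with a p-value floor of 0.125, and a pair-level analysis has about 48% to 56% power. In that case only, district-level tests could have false-positive rates of about 7% to 18%, and only if a quarter or more of the between-district variance is common to a group.

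These figures assume a two-sided 5% test, an ICC of 0.01 and 15% loss. The false-positive rates and the single-district counts also assume municipalities of 4, 4, 4 and 5 districts.

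**What to change.** 1. Obtain the allocation record from the independent data manager. Correct the Randomisation text to say what was drawn, how the two groups were formed if they existed before the draw, and how many allocations were admissible.
2. On either reading, include municipality as a block and 2015 expected births as a covariate in the primary analysis. Report a re-randomisation p-value over the admissible allocations beside the model result.
3. Only if pre-formed groups were allocated, describe the design as eight allocation units in four pairs, make the allocation group the top clustering level with matching small-sample degrees of freedom, and restate the power. The 16-allocation p-value is then supporting information, since it cannot fall below 0.125.
4. If single districts were drawn, reword the sentence on dividing districts into two groups and keep the district as the clustering level.

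The cost is wording, a little analysis code and a few degrees of freedom. If groups were allocated, intervals will be wider and the stated power lower. No new participants or data are needed.
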